**Fig 1 pone.0304630.g001:**
[figure not shown]
Flow diagram with BOOST study procedures and timeline.

**Table 1 pone.0304630.t001:** Participant timeline.

	Week										
	0	1	2	3	4	5	6	7	8		16–40
**Visit 0: Baseline**	X										
Shared Reading Video 1	X										
Video Recorded Speech Task	X										
Shared Reading Frequency Survey	X										
Family Demographic Information	X										
Child Medical/Developmental History Interview/Chart Abstraction	X										
MacArthur Bates Communicative Development Inventory CAT	X										
**Randomization**	X										
Shared Reading Frequency Surveys (5x per week, randomly selected days)		X	X	X	X	X	X	X	X		
Shared Reading Video 2			X								
**Visit 1 (BOOST TREATMENT GROUP ONLY)**				X							
Shared Reading Video 3					X						
**Visit 2 (BOOST TREATMENT GROUP ONLY)**						X					
Shared Reading Video 4							X				
**Visit 3 (BOOST TREATMENT GROUP ONLY)**								X			
Shared Reading Video 5									X		
**Visit 4: Final Assessment**											X
Expressive One-Word Picture Vocabulary Test-4											X
Receptive One-Word Picture Vocabulary Test-4											X
MacArthur Bates Communicative Development Inventory CAT											X
Video Recorded Speech Task											X
Video Recorded Child Language Sample											X
Shared Reading Frequency Survey											X

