### Statistical methods

In analyses for our primary outcomes, we will use an intention-to-treat (ITT) approach to test the hypothesis that children in the BOOST group exhibit better language skills than children in the SCO comparison group. We will calculate 2-sample unequal-variance t-tests to estimate treatment versus control group differences in child language outcomes post-intervention. We will calculate standardized treatment effect sizes (ES) for all analyses to allow comparison across outcomes with different measurement scales. We will not adjust for covariates in the primary analyses. However, in sensitivity analyses, we will use bias-corrected ITT analyses to examine the robustness of treatment effects in the setting of non-adherence, missing data, or study attrition. To assess attrition bias, we will explore outcomes using Inverse Probability Weighting (IPW), with weights determined by the probability of having missing data or being lost to follow-up based on the RCT stratification variables and demographic and clinical data [39]. We will also conduct sensitivity analyses to examine the effects of variation in treatment fidelity using a weighting approach. Finally, we will examine the potential effects of children’s participation in other interventions in the community (e.g., speech and language therapy) using censored normal regression (CNR) [40].

Longitudinal analyses examining changes in child language during book-sharing and caregiver behaviors (i.e., quality and frequency of book-sharing) will use a GEE approach to linear regression with robust standard error estimates. This approach accounts for the correlation of observations over time and allows for the use of partial data on subjects who are lost to follow-up or non-compliant. Estimates will be adjusted for the RCT stratification variables, demographic confounds, and clinical characteristics (e.g., cleft type, age at cleft repair). Smoothing splines will be fit to examine changes in parents’ reading behaviors over time, including non-linear trends.

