We will use a multi-step linear regression approach to examine whether changes in parents’ reading behaviors mediate differences in children’s language outcomes. Mediators include: (1) shared reading frequency, (2) overall quality of parent-child interactions, and (3) parents’ shared reading skills, which will be assessed throughout the intervention period. Mediators will be analyzed separately to determine their individual effect on child outcomes and to avoid a washout effect from including all mediators in a single model. We will not adjust for multiple comparisons for this aim. Each regression model will follow the same basic approach to analyzing the effects of adjustment for a given mediator (Z) on the association between the intervention (X) on the child language outcome (Y). We will run two models per outcome: (1) Y = α + βX + e1, and (2) Y = A + BX + CZ + e2. The terms e1 and e2 represent model errors. Model 1 describes the unadjusted effect of the intervention on the outcome. Model 2 illustrates the combined effect of intervention and mediator on outcome. A comparison of the coefficients β and B indicates the degree of mediation. For example, β = B >0 suggests a positive intervention effect that is not mediated by Z (i.e., the null hypothesis of no mediation), whereas β >0 and B = 0 reflects a positive effect fully mediated by Z. Intermediate values reflect the degree of mediation (e.g., B = β/2 represents 50% mediation). Confidence intervals for the degree of mediation will be obtained using the bootstrap methods.

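### The mediation regressions contain only arm and mediator, so baseline factors that affect both parental reading and child language can bias the estimated degree of mediation, most plausibly upward

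*Protocol article*

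**What the plan says.** The Objectives in the Abstract list mediation as the second of two primary hypotheses. Statistical methods gives the models: "1) Y = α + βX + e1, and (2) Y = A + BX + CZ + e2", where X is arm, Z the mediator and Y the child language outcome. On their content it says "Model 1 describes the unadjusted effect of the intervention on the outcome" and "Model 2 illustrates the combined effect of intervention and mediator on outcome". The reading rule is "A comparison of the coefficients β and B indicates the degree of mediation", with B equal to half of β read as 50% mediation and bootstrap confidence intervals for the degree of mediation. All three mediators (reading frequency, interaction quality, parents' shared reading skills) are handled alike: "Each regression model will follow the same basic approach to analyzing the effects of adjustment for a given mediator (Z"). They are analysed one at a time, without multiplicity adjustment.

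Covariates do appear one paragraph earlier in the same section: "Estimates will be adjusted for the RCT stratification variables, demographic confounds, and clinical characteristics (e.g., cleft type, age at cleft repair"). That sentence concerns the longitudinal GEE analyses and is not carried over to the mediation models. The week 0 column of Table 1 includes "Shared Reading Video 1", the reading frequency survey, the speech task, family demographics and the CDI-CAT.

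**The concern.** The mediator is measured after randomization and is not itself randomized. Parents with more education, or with more verbal children, may read more and better, and their children may score higher whatever the parents do. With no covariate in model 2, coefficient C takes up that association, and β − B takes it up with C. The bootstrap describes sampling error around this quantity and does not remove the bias.

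The article itself points to one such factor. Under Speech production accuracy and sound diversity it hypothesizes that speech at baseline may affect how caregivers respond to the child. Speech at baseline may well be related to later measured language too.

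At stake is the answer to the second primary hypothesis: a share of the treatment effect could be credited to reading frequency or quality that did not cause it, or a real pathway could be missed.

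**Working it through.** **Figures in the plan.** The mediation text gives no numerical target, and its claim of more than 80% power has no inputs, so there is no mediation figure to reproduce. The primary comparison can be checked: 128 per arm, two-sided alpha 0.025 and a difference of 0.4 SD give 83.1% power (normal) or 82.7% (t). The detectable difference at 80% power is 0.387 SD. Both agree with the stated 80% for 0.4 SD, so about 256 analysed children is a sound basis here.

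**Inputs.**
- Arm effect on the mediator, a = 1.0 SD, and on child language, β = 0.4 SD (Introduction, from meta-analyses of dialogic book-sharing).
- N = 256 (sample size section).
- True effect of Z on Y: zero, so the true mediated share is 0%.
- One baseline factor U with within-arm correlations r_UZ with the mediator and r_UY with the outcome. These are assumptions; the documents give none.
- Z is the raw post-randomization level.

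**Formula.** In least squares, β − B = a × C. If Z has no effect on Y, then C = r_UZ × r_UY within arm, in unit SDs. The false mediated share is therefore (β − B)/β = a × r_UZ × r_UY / β.

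| a | r_UZ / r_UY | β − B | False share |
|---|---|---|---|
| 1.0 | 0.2 / 0.2 | 0.04 | 0.04/0.4 = 10% |
| 1.0 | 0.3 / 0.3 | 0.09 | 0.09/0.4 = 22.5% |
| 1.0 | 0.3 / 0.5 | 0.15 | 0.15/0.4 = 37.5% |
| 1.0 | 0.4 / 0.5 | 0.20 | 0.20/0.4 = 50% |
| 0.5 | 0.3 / 0.5 | 0.075 | 0.075/0.4 = 18.75% |
| 0 | any | 0 | 0% |
| 1.0 | −0.3 / 0.5 | −0.15 | −0.15/0.4 = −37.5% |

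**Check by simulation.** With 300 trials per case and 200 bootstrap resamples per trial, the mean false shares at a = 1.0 were 23.5% (0.3/0.3), 36.5% (0.3/0.5), 49.8% (0.4/0.5) and −37.6% (−0.3/0.5). In the first three of these cases the 95% bootstrap interval wrongly excluded zero in 32%, 68% and 92% of trials, against 3% with no confounder. A separate run of 3,000 trials per case gave a median share of 9% at 0.2/0.2.

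**After adjustment.** With U in both models, mean β − B lay between −0.004 and 0.007 in all cases. In the confounded cases where the arm moves Z, the interval excluded zero in 4% to 8% of trials. Here U is the only confounder and is measured without error, so this shows the best that adjustment can do.

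**The case against.** Several counterarguments have force.

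- **Direction.** A reader might infer that confounding will be reported as mediation. The documents do not support that certainty. The sign follows the product of two unknown correlations; if, for example, parents read more to children who talk less, mediation would be hidden. Measurement error in the mediator also pulls the estimate down: with an assumed reliability of 0.6, no confounding and a true share of 50%, the expected estimate is about 0.6 × 50% = 30%.
- **Change scores.** The mediation paragraph opens by speaking of changes in parents' reading behaviours. If Z is change from baseline and the confounder acts equally on both measurements, it cancels: the same scenarios then give a median false share of about 0% with 4% positive tests. This is a plausible reading, but the equations do not define Z that way, and unequal loading would leave some bias.
- **The word unadjusted.** A reader might take it as proof that covariates are ruled out. In that paragraph adjustment refers to adjustment for Z, so model 1 may be called unadjusted only because it lacks Z. The evidence is the equations themselves. A fuller covariate list could stand in an analysis plan that is not shown, but the article writes the models out and includes none.
- **Size.** Weaker correlations give less: 0.1/0.3 yields 0.03/0.4 = 7.5%. The effect of 1.0 SD is quoted for reading behaviours in general and need not hold for every mediator.
- **Instability of the percentage mediated.** A reader might call this a defect too. The planned bootstrap interval would already show it as width, so it is a reporting preference.
- **Standing of the analysis.** The sample size rests on the group comparison, and the mediators are listed under Intermediate and exploratory outcomes. That lowers the severity, although the Objectives still name mediation as a primary hypothesis.

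What survives is that the path from mediator to outcome is left open in the models as written.

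**Conclusion.** The point holds as a risk of bias whose existence does not depend on exact values but whose size does. Two conditions produce it: the arm shifts the mediator, as the article expects, and some baseline factor is related to both mediator and outcome. With effects of 1.0 and 0.4 SD, a raw post-randomization mediator and assumed correlations of 0.2/0.2 to 0.4/0.5, a true share of 0% reads as about 10% to 50%. At −0.3/0.5 the bias is about −37%. Upward bias is the more plausible direction but is not assured.

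It would be wrong to go further and say that the trial is bound to confirm mediation falsely, or that its efficacy conclusion is compromised. The primary comparison is an unadjusted contrast of randomized groups and does not involve the mediator. Severity: should be fixed.

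**What to change.** Enter the same prespecified baseline covariates W in both models, fitted to the same children: Y = α + βX + γW + e1 and Y = A + BX + CZ + ΓW + e2. W would contain:
- the baseline value of the mediator (Video 1 score or baseline reading survey);
- baseline CDI-CAT;
- baseline speech task score;
- child age and parent education;
- the stratification factors site, preferred language and Medicaid status.

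State whether Z is a post-randomization level or a change from baseline. State also that adjustment removes measured confounding only: baseline language is parent-reported expressive vocabulary, and Table 1 lists no receptive test at week 0. For that reason, add a sensitivity analysis showing how strong an unmeasured confounder of mediator and outcome would have to be to remove or reverse the estimate. Reporting β − B with its bootstrap interval beside the percentage mediated is an optional addition.

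The cost is a paragraph of analysis-plan text and a few lines of code. The covariates are collected at week 0 or known at randomization. With three sites, and age and education as single terms, W has about 2 + 1 + 1 + 5 = 9 terms, which about 256 children can support. Neither the sample size nor the primary analysis changes.

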## Materials and methods

### Study setting

We have three participating study sites in Washington (WA), California (CA), and Ohio (OH), all with active cleft and craniofacial teams in tertiary-care hospital settings. We seek to enroll a sample that is representative of the demographic characteristics of our patient populations. For example, 37% to 60% of the patients seen in our centers receive Medicaid funding for their healthcare. Approximately 18% of our patients are Latino/Hispanic, and 27% are non-white. After English, Spanish is the most common language spoken by families. Therefore, we translated study materials and ensured that our team included bilingual/Spanish-speaking staff to facilitate the inclusion of Latino/Hispanic families. Translation procedures included initial translation by an outside service and independent back-translation by a separate translator who had not seen the original English versions. Bilingual/Spanish-speaking investigators from our team and content experts then reviewed all translated materials. We made final modifications to ensure the original meaning was retained and that translations were appropriate for a broad Spanish-speaking population. In some instances, we revised the wording of English materials to ensure comprehension and consistency across languages.

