### Sample size considerations and participant recruitment and retention

We determined the sample size (N = 320) based on the number of participants needed to ensure 80% power to test the hypothesis that children in the BOOST intervention group will have better receptive and expressive language skills than those in the SOC comparison group. Power analyses were based on two-sample unequal-variance t-tests, an alpha = 0.05/2 to adjust for multiple comparisons, and up to 20% attrition (i.e., final N~256). Under these assumptions, we will have 80% power to detect treatment group differences of >0.4 SD for our primary outcomes. Treatment effects this large have been observed in DBS studies with other non-cleft populations and are considered plausible and clinically meaningful [13].

Our assessment of longitudinal changes in child language during book-sharing interactions (Hypothesis 1b) will use a generalized estimating equations (GEE) approach to linear regression with robust standard error estimates. The outcome for these analyses will be observed child language, calculated as an average number of utterances, unique words used, and mean length of utterance. Analyses will test the effects of the intervention on children’s language during book-sharing interactions over the five observations. We will have > 80% power to detect changes with an effect size > 0.4 between any two time points and changes with effect sizes > 0.3 overall. Meta-analyses of similar interventions with non-cleft participants suggest that effect sizes this large or larger are observed and considered clinically meaningful. Similarly, we will have > 80% power to assess longitudinal changes in children’s language during book-sharing interactions, the quality and frequency of book-sharing interactions, and changes in parents’ book-sharing behaviors as a mediator of differences in children’s language outcomes.

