Finally, we will explore demographic and clinical characteristics associated with "good" versus "poor" treatment responses. In these analyses, we will examine parent reading behaviors and child outcomes in relation to clinical and demographic characteristics (e.g., language spoken in the home, family composition, parents’ education level, the child’s cleft type, child’s hearing status, sex of the child, study center/interventionists). We will use a two-step process for model selection and analysis. First, we will identify children who score > 0.5 SD above or below the mean relative to their intervention group. Second, we will examine the distribution of each characteristic of interest and identify those that (a) differ in distribution between those who score above-expected values, below-expected values, and as-expected and (b) have sufficient cell sizes (n >30). Selected variables will then be included in multivariate linear regression models to evaluate whether parents’ reading behaviors and child language outcomes vary across subgroups. We will calculate correlations between each variable before fitting any model, combining or excluding variables to avoid multicollinearity. To prevent overfitting, no more than 12 terms will be included in the model.

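### The exploratory treatment-response analysis screens characteristics on a three-class cut of a continuous score, which loses power before a regression that uses the full scale, and its n > 30 cell rule can be read two ways

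*Protocol article*

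**What the plan says.** The last part of Statistical methods in the Protocol article looks at who responds well or poorly. It is framed as exploratory: "we will explore demographic and clinical characteristics associated with" good or poor response. The candidates it lists include home language, cleft type, hearing status, the child's sex, and study center or interventionist.

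Selection has two steps:

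- **Classing.** "First, we will identify children who score > 0.5 SD above or below the mean relative to their intervention group". This gives three classes: above, below and as expected.
- **Selecting.** A characteristic is kept if its categories "differ in distribution between those who score above-expected values, below-expected values, and as-expected" and if they "have sufficient cell sizes (n >30").

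Then: "Selected variables will then be included in multivariate linear regression models" of parents' reading behaviors and child language outcomes, with at most 12 terms and a check for collinearity.

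The text does not say which test or threshold decides that distributions differ, or whether a cell is a class-by-level combination or a whole level.

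Two other places supply figures. The sample size section allows for "up to 20% attrition (i.e., final N~256"). Study setting describes three sites and states: "Approximately 18% of our patients are Latino/Hispanic, and 27% are non-white". Neither the home-language share nor the split across sites is given.

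**The concern.** The language scores are continuous and the final model analyses them as such. The three classes play no part in that model; they only decide which characteristics may enter it. Cutting a score at ±0.5 SD treats a child just above the cut and a child far above it as the same, so a real difference in means is harder to see at the gate than in the model behind it. A characteristic stopped there never reaches the full-scale analysis, so the regression cannot recover it. No reason for the cut is given.

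The cell rule may add to this. If n > 30 must hold in every class-by-level cell, the cut divides each level's children over three columns, and levels with adequate totals can fail. Home language and study center are on the article's own list of interest, and preferred language and site are stratification factors in the randomization.

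**Working it through.** **Inputs.** From the article: N = 320 randomized, about 256 analysed after 20% attrition; cuts at ±0.5 SD of the child's own group mean; n > 30; three sites; 18% Latino/Hispanic. Assumed: a normal score; 18% as a proxy for the smaller home-language level; equal-sized sites; a two-sided 5% screen unless stated; a difference in means between levels.

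**The plan's own figure.** No power is stated for this analysis. The nearest figure is the primary one: 80% power for more than 0.4 SD at alpha 0.05/2. With 128 per arm the normal approximation gives 83% at 0.4 SD, and 80% power is reached at (2.241 + 0.842) × √(2/128) = 0.385 SD. The stated figure is slightly conservative, and N = 256 is a fair basis for what follows.

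**Class sizes.** P(Z > 0.5) = 0.3085. Each outer class holds 0.3085 × 256 = 79 children and the middle class 0.3829 × 256 = 98. At N = 320 these are 99 and 123.

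**Power of the screen.** Simulation at N = 256, two equal arms, score standardized within arm, characteristic with two levels. The columns compare a t-test on the score, a 2-df chi-square on the three classes, and a trend test on the classes, all at 5%.

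| Share of smaller level | Difference | Continuous | Chi-square | Trend |
|---|---|---|---|---|
| 50% | 0.35 SD | 79% | 59% | 70% |
| 50% | 0.40 SD | 88% | 73% | 82% |
| 33% | 0.35 SD | 75% | 54% | 65% |
| 18% | 0.40 SD | 68% | 49% | 59% |
| 18% | 0.45 SD | 79% | 59% | 70% |

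- Chi-square at 5%: a loss of about 15 to 21 points in these rows. With equal levels it narrows to about 12 points at 0.20 SD (36% vs 23%) and 7 at 0.50 SD (98% vs 91%).
- Trend test at 5%: about 7 to 10 points in these rows, and about 3 at 0.50 SD.
- Chi-square at a 20% threshold: 93% vs 83% (equal levels, 0.35 SD), 98% vs 90% (equal levels, 0.40 SD) and 87% vs 74% (18% level, 0.40 SD), a loss of about 7 to 13 points.
- A three-level factor such as site, analysis of variance against a 4-df chi-square at 5%: 74% vs 53% and 86% vs 67% for two patterns of means.

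**Cell rule, class by level.** The expected count in an outer class is N × 0.3085 × share.

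- Share needed at N = 256: 30 / 79.0 = 38%. At N = 320: 30 / 98.7 = 30%.
- 18% level: 0.18 × 79.0 = 14 at N = 256 and 0.18 × 98.7 = 18 at N = 320. It fails at both.
- One of three equal sites: 79.0 / 3 = 26 at N = 256 (fails) and 98.7 / 3 = 33 at N = 320 (passes). The crossing point is 30 × 3 / 0.3085 = 292 children, or attrition of about 9%.

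**Cell rule, level total, N = 256.** 18% level: 0.18 × 256 = 46. Equal third: 256 / 3 = 85. Both pass.

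**The case against.** The strongest reply is that much of the size rests on choices the article does not make. It names no screening test and no threshold, and looking for a difference in distribution could be partly descriptive. Those details belong to an analysis plan that is not shown. This stands: no single power loss can be attributed to the plan, and the figures hold only for the screens named. What remains is that the cut itself is fixed in the article, and every screen tried on the classes had less power for mean differences than the continuous score.

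A reader might infer that the rule as written shuts out home language and study center. The document does not support that. It does not define a cell; on the level-total reading both pass at the assumed shares. Even on the class-by-level reading, equal sites pass at N = 320, and 256 is the figure at the upper bound on attrition. An unequal split would leave the smallest site worse off, but the split is not stated. For home language, 18% is an ethnicity share used as a proxy. If the true share were below 30 / 256 = 12%, the level total would fail too, and the cause would then be too few children and not the cut.

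A second reply is that the classes ask who lies in the tails. For a characteristic with equal means but an SD ratio of 1.6 between two equal levels, the three-class chi-square has about 72% power and a mean-based screen only about 5 to 6%. That is true, and it is a real cost of changing the screen. It is a weak defence of the cut here, because the regression that follows also models means and would not show such a characteristic as an effect.

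Finally, the analysis is exploratory and carries no confirmatory claim. That limits the importance of the point without removing it.

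**Conclusion.** The point holds in a limited form. The gate uses a three-class version of a score that the next step analyses in full, and for mean differences this costs power: about 15 to 20 points at about 0.35 to 0.45 SD and N of about 256 under a three-class chi-square at 5%, and about 5 to 13 points with a trend test or a looser threshold. These figures assume a normal score.

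The exclusion of named characteristics is possible but not established. It depends on reading a cell as class by level, on the 18% proxy for home language, and on the unstated site split. On that reading home language may be excluded and study center is borderline; on the other reading neither is excluded at these shares.

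This is a cheap improvement to an exploratory analysis. The primary comparison is not affected.

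**What to change.** In the treatment-response part of Statistical methods, or in the analysis plan:

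- Screen each listed characteristic against the continuous score, either centred on the child's group mean or through the linear model already planned for the second step.
- State that n > 30 applies to the number of analysed children in each level of the characteristic.
- Keep the 12-term limit and the collinearity check.
- Keep the above, as-expected and below classes as a descriptive display only.

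The cost is a change of wording; no new data, participants or staff are needed. There are three small downsides: the good-versus-poor grouping no longer drives selection, more candidates may compete for the 12 terms, and a mean-based screen will not pick up a characteristic that affects only the spread of scores.

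### The treatment-response exploration ranks children by outcome level within their own arm, so it cannot tell effect modifiers from prognostic factors

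*Protocol article*

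**What the plan says.** The last paragraph of the Protocol article's Statistical methods section opens "Finally, we will explore demographic and clinical characteristics associated with" good as against poor treatment responses. The candidates, given as examples, are "language spoken in the home, family composition, parents’ education level, the child’s cleft type, child’s hearing status, sex of the child, study center/interventionists".

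The procedure has two steps:

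- **Classification.** "First, we will identify children who score > 0.5 SD above or below the mean relative to their intervention group".
- **Selection and modelling.** Characteristics are kept if they "differ in distribution between those who score above-expected values, below-expected values, and as-expected and (b) have sufficient cell sizes (n >30"). Then: "Selected variables will then be included in multivariate linear regression models to evaluate whether parents’ reading behaviors and child language outcomes vary across subgroups".

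The stated safeguards are the cell-size rule, a check for collinearity, and a cap: "To prevent overfitting, no more than 12 terms will be included in the model". No comparison between arms, arm-by-characteristic interaction, correction for the outcome-based selection or validation in other children is described.

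**The concern.** In a parallel-group trial, information on who benefits comes from comparing arms within levels of a characteristic. A child who scores above the mean of his or her own arm is a high scorer, which is not the same as a child who gained from the programme. For the EOWPVT-4 and ROWPVT-4 the class cannot even reflect change, because Table 1 schedules both tests only at the final assessment.

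Several named candidates (parental education, hearing status, sex) could plausibly relate to toddler vocabulary whether or not a family receives BOOST. The procedure would tend to report such factors as markers of treatment response.

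A second problem is double use of the data. Characteristics enter the model because they differ across outcome classes, and are then tested against that outcome in the same children. The 12-term cap limits the final model and does not undo the screening. This applies directly to child language. For parents' reading behaviours it is at most indirect, unless classes are also formed on those scores, which the text does not say.

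**Working it through.** **Inputs from the article.** The sample size section gives "an alpha = 0.05/2 to adjust for multiple comparisons, and up to 20% attrition (i.e., final N~256"). With 1:1 allocation that is 128 analysed per arm. The class boundary is 0.5 SD from the own-arm mean.

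**The plan's own figure.** None is given for this analysis. As a check on the sample size used here, 128 per arm at two-sided alpha 0.025 gives a detectable difference at 80% power of (2.241 + 0.842) × √(2/128) = 0.385 SD, in line with the stated 0.4 SD.

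**Assumptions, not in the article.** Normal outcome with SD 1; binary characteristic; screen by chi-square across the three classes at p<0.05; both arms pooled; final regression on arm and characteristic, tested at p<0.05. The n >30 rule is not applied per level-by-class cell. Rates are from about 2,000 to 8,000 simulated trials per scenario.

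**Why the rule misses the target.** Let a characteristic x have prognostic effect g in both arms, and let the BOOST effect be d0 when x = 0 and d1 when x = 1. With equal arms and no interaction term, the expected coefficient on x is

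g + (d1 − d0)/2.

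The quantity that defines a modifier is d1 − d0. The formula mixes it with g, and the analysis has no means of separating them.

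**Case 1: prognostic only** (30% prevalence, g = −0.5, d1 = d0). The expected coefficient is −0.5.
- Selected in 83 to 84% of runs when BOOST has a uniform effect of 0.4 SD.
- Selected in about 83% when BOOST has no effect.
- An arm-by-x interaction test is significant in about 5% in both settings.

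**Case 2: true modifier** (50% prevalence, d0 = 0, d1 = 0.8).

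| g | Expected coefficient | Selected and significant | Interaction test |
|---|---|---|---|
| 0 | 0 + 0.4 = 0.4 | about 68% | 88–90% |
| −0.4 | −0.4 + 0.4 = 0 | about 2% | 88–90% |
| −0.8 | −0.8 + 0.4 = −0.4 | about 68%, sign reversed | 88–90% |

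In the last row the group that gains most from BOOST is reported as the poor-response group.

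**Case 3: null characteristic.** At 40% prevalence it passes the screen in about 5% of runs. Once it has passed, it reaches p<0.05 in the final model about 39% of the time. Unconditionally it is both selected and significant in about 0.05 × 0.39 = 2% of runs. With seven null characteristics, at least one false finding occurs in 13.5% of runs.

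**The replacement.** With a 50%-prevalence moderator there are 64 children in each of four arm-by-level cells, so the SE of the interaction is √(4/64) = 0.25. For an interaction of 0.4 SD, 0.4/0.25 = 1.6 and power is Φ(1.6 − 1.96) = 36%. Seven unadjusted tests at 5%, taken as independent, give 1 − 0.95^7 = 30% chance of at least one false positive.

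**The case against.** The strongest reply is that this is labelled as exploration, affects neither the primary test nor the sample size, and appears in a condensed article whose SAP is not shown. The final model's terms are not listed, so an interaction could be among them. The low stakes stand. The SAP argument does not rescue the procedure, because the classification and the screen are fixed in the article: an interaction added later would be fitted only for characteristics already chosen on outcome level.

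The text could also be read as applying to BOOST children only. The problem remains. A 50%-prevalence factor worth 0.5 SD, with no BOOST effect, is still selected and significant in 58% of runs, and the Case 2 modifier is found in 96%, 39% and 2% as its prognostic effect goes from 0 to −0.4 to −0.8 SD.

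Four stronger readings may tempt a reader, and the documents do not support them:

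- **That the procedure can never find who benefits.** It finds a modifier with no prognostic effect in about 68% of runs. What it cannot do is distinguish modifiers from prognostic factors.
- **That SOC children are called responders.** The text speaks of scores above, below or as expected and does not say how the arms are combined.
- **That the rule "have sufficient cell sizes (n >30") removes subgroups the plan names.** What counts as a cell is undefined, and no home-language prevalence is given. On a level-by-class reading, the 30%-prevalence factor in Case 1 would never pass; on a per-level reading, its 83% stands. No conclusion is drawn from this rule.
- **That 39% is the false-positive rate.** It is conditional on passing the screen. The replacement has more chance findings across seven tests if left unadjusted (30% against 13.5%). Its advantage is that it tests the right quantity.

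The article also does not say that these results will be used to decide which families are offered BOOST.

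**Conclusion.** The point holds in limited form. The stated rule does not match its stated aim: it sorts children by outcome level within arm and so cannot distinguish effect modification from prognosis. That follows from the expected coefficient and needs no simulation. The simulated rates show the size of the problem and depend on the assumed prevalence, effect sizes and screening threshold, none of which the article gives. For child language outcomes, the final-model p-values are also invalid after selection on the same outcome. The consequence is confined to one exploratory analysis; it should be corrected, but it does not threaten the trial's main conclusion.

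**What to change.** Drop the ±0.5 SD classes and the outcome-based screen. Name a short list of moderators in advance, drawn from the characteristics already in the article. Test each by an arm-by-moderator interaction on the continuous outcome in all analysed children, adjusted for baseline CDI-CAT, which Table 1 already schedules. Report interaction estimates with confidence intervals and label them exploratory. Either adjust for multiplicity or state the roughly 30% chance of at least one false positive over seven unadjusted tests. State also that power is about 36% for a 0.4 SD interaction with a 50%-prevalence moderator, before any gain from baseline adjustment.

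The cost is a change of wording in the analysis plan; no new data are needed. The drawback is that the wide intervals will show plainly how little the trial can say about moderation.
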